### Data management and availability

The study adheres to the General Data Protection Regulation (GDPR) and the Data Protection Act 2018, which mandate that data be de-identified as soon as reasonably possible. All data collected in this study will be anonymised, with each participant assigned a unique study code. Personal information will be securely stored in locked filing cabinets at the principal investigators (AG) office at Northumbria University and will only be accessible to the research staff directly involved in the study. Data will be entered into an electronic database using the unique study codes and securely stored on a password-protected computer. Any significant protocol changes during the study will be reported to the trial registry. The de-identified participant data that support the findings of this study will be available from the Northumbria University Research Ethics Committee. Access requires approval from the Committee and a signed data-sharing agreement. Requests should be sent to the corresponding author, AG ([contact]), who will coordinate requests with the Committee.. The findings will be shared through academic outputs, including national and international conferences and publications.

## Discussion

The protocol outlined for the validation and exploration of CuePD, a proposed approach to scale assessment and retraining in gait rehabilitation for PwPD. It adopts a novel approach by integrating personalised auditory cues through pervasive smartphone technology. This method diverges significantly from traditional rehabilitation strategies by emphasising a user-centric approach to enhance engagement and encourage long-term use in PwPD.

### Clinical validation

Previous CuePD studies have established validity within non-clinical cohorts [61,62] but this protocol aims to establish the validity of temporal, spatial, and spatiotemporal gait characteristics in PwPD compared to an established gold/reference-standard wearable. Establishing robust validity is essential to ensure reliable measurements, which are critical for the effective administration of targeted and personalised cueing interventions that often lead to more significant improvements in gait [81,82].

### Primary objectives: Validity and evaluating the effects of personalised auditory cues on gait

The impact each personalised auditory cue has on participants’ stride length, gait speed, and${\text{ CV}}_{\text{stride}-\text{time}}$ are a significant exploratory interest. These metrics, in particular${\text{ CV}}_{\text{stride}-\text{time}}$, where a decrease is known to reduce the risk of falling, have indicated variable effects among PwPD in other cueing-related studies, particularly where music cueing is not personalised [9,44,73]. The findings from this study will establish a baseline understanding of their (i) validity (from an app and smartphone worn on the lower back) and (ii) whether personalised cues can consistently reduce stride variability across a broader range of participants.

Observed gait responses will be interpreted in the context of sequence-conditional effects (cue order, exposure, and adaptation over time), and not as definitive evidence of causal superiority of one cueing condition over another. Analyses of gait variability and asymmetry will be interpreted cautiously, as these measures typically exhibit greater dispersion and may be underpowered (as sample size of based on gait speed). Emphasis will be placed on estimating effect sizes and examining consistency of responses across conditions, rather than on formal hypothesis testing.

### Exploratory objectives: preference, usability, and musicality

Exploratory objectives of the protocol also focus on the user experience and the clinical efficacy of the personalised auditory cues provided by CuePD. A significant part of this exploration involves understanding the preferences of PwPD for engaging with personalised music cues during routine walking exercises, compared to traditional metronome cues which are often perceived as monotonous and less engaging. This preference for music could play a crucial role in enhancing patient engagement and adherence to the rehabilitation process. Finally, the study explores how well patients’ musicality correlates with their ability to synchronise with the auditory cues. If no relationship is found, this would indicate that the success of music cueing-based interventions does not depend on a patient's inherent musical skills, potentially broadening the applicability of such treatments to a wider demographic of PwPD.

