
After completion of all walks, participants will complete:

(viii)**Goldsmiths Musical Sophistication Index (Gold-MSI)**: A 39-item (scored from 1 to 7) self-report designed to assess musicality across five subscales: active engagement (AE), perceptual abilities (PA), musical training (MT), singing abilities (SA), and emotional response (ER) to music [70]. This tool evaluates and provides the detailed extent and nature of musical experiences and skills, but also provides a broader score on musicality, General Music Sophistication (GMS), ranging from 32 to 126. For this study, the scale will be used to assess if there was a relationship between an individual’s general music sophistication and their adherence to the beat of the music cues. Furthermore, the relationship between an individual’s subscale results and beat adherence will also be assessed.(ix)**System Usability Scale (SUS):** This will evaluate perceptions of the app’s usability, complexity, and overall satisfaction [71]. The SUS produces a composite score that ranges from 0 to 100, calculated by first adjusting the responses from a set of ten questions. For odd-numbered questions, the process involves subtracting one from each score, whereas for even-numbered questions, the score is subtracted from five, resulting in adjusted values that fall between 0 and 4. These adjusted values are subsequently summed together, and the total is multiplied by 2.5 to derive the final SUS score, with higher scores reflecting superior usability.(x)**Cueing preference:** Lastly, participants are asked a question to determine preferred cueing modality, “Which cueing do you prefer, was it metronome, instrumental music or vocal music?”

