**Walk #2:**
iThe participant navigates the same 25m loop while allocated to a sequence (above) set at +10% of their baseline cadence (walk #1).iiInstructions to the participant: Walk to the beat of the cue.iiiWO1 (Part 1: sitting and counting backwards followed by Part 2: 1-minute walk at self-selected pace)c

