#### Adherence to cues and musicality.

Adherence will be treated both as a continuous variable (percentage change in cadence from baseline) and as a binary variable for group comparisons. The primary binary adherence definition is: adherent = ≥5% increase in cadence from baseline; non-adherent = < 5%. Mann–Whitney U tests will compare Gold-MSI between adherent and non-adherent participants. Participants with missing baseline or intervention-based cadence (e.g., wishing to withdraw or technology failure) will be excluded from binary adherence analyses and numbers excluded will be reported.

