To evaluate the relationship between musical sophistication and response to cueing, two sets of analyses will be conducted using Gold-MSI subscale scores. Assumption checks, including the Shapiro-Wilk test and Q-Q plot inspections, will be used to assess the distribution of change scores prior to both analyses. First, the association between Gold-MSI scores and cue adherence (defined as the absolute deviation from a + 10% target increase in cadence) will be assessed using Spearman’s rank correlation coefficient, with Bonferroni correction for multiple comparisons across subscales. Second, associations between Gold-MSI scores and gait outcome improvements (percentage change in gait speed and stride length, and log-ratio change in ${\text{CV}}_{\text{stride}-\text{time}}$) will also be tested using Spearman’s correlation, with Bonferroni correction.

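### The musicality objective is worded as synchronising with the beat, but adherence is only cadence change per walk, so its conclusion should be limited to average tempo matching

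*Protocol article*

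**What the plan says.** Three places in the protocol article describe following a beat:

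- Data collection, item (viii) Gold-MSI: the scale will be related to participants' "their adherence to the beat of the music cues".
- Walking/gait tasks, each cued walk: the instruction is "Walk to the beat of the cue".
- Discussion, Exploratory objectives: the study explores how well musicality "correlates with their ability to synchronise with the auditory cues". It continues: "If no relationship is found, this would indicate that the success of music cueing-based interventions does not depend on" inherent musical skill.

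The measures are defined elsewhere, all from cadence:

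- Outcome measures, Adherence to cues and musicality: "Adherence will be treated both as a continuous variable (percentage change in cadence from baseline", and a binary rule, "adherent = ≥5% increase in cadence from baseline; non-adherent = < 5" per cent, used for Mann–Whitney comparisons of Gold-MSI.
- Statistical analysis: one percentage change in cadence per participant and cueing modality.
- Statistical analysis, Gold-MSI paragraph: "cue adherence (defined as the absolute deviation from a + 10% target increase in cadence", correlated with Gold-MSI by Spearman's coefficient.

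No step-to-beat timing or phase measure is defined. The same Gold-MSI paragraph plans a second set of Spearman correlations, between Gold-MSI and changes in gait speed, stride length and stride-time variability.

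**The concern.** Cadence says how fast a person stepped, not whether the steps kept to the beat. Someone who simply walks faster can raise cadence without following the cue, and cadence also depends on physical capacity to speed up. A null correlation between Gold-MSI and cadence change could therefore arise because the measure does not capture synchronisation. The Discussion nevertheless commits in advance to reading a null as evidence about musical skill and the success of cueing. The article itself fixes both the definitions and the interpretation, so this is not a detail left to an analysis plan.

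**Working it through.** The plan gives no figure on this point, so there is nothing to reproduce. The check applies its own rules to idealised walks.

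**Inputs**
- Cue tempo = 1.10 × baseline cadence; walk length 1 minute (Walking/gait tasks).
- Binary rule: adherent at +5% or more, no upper limit (Adherence to cues and musicality).
- Deviation score D = |percentage change in cadence − 10| (Statistical analysis).
- Baseline cadence is not given. Assumed 100 steps/min, with 90 to 120 as the range.
- Cadence is taken as one value per walk. The article does not say so in words; it follows from one-minute sessions processed after they end (Smartphone and CuePD) and one change per modality.

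**Formulas**
- Beats slipped in the minute = cue beats/min − steps/min.
- Step-to-beat consistency R = |mean of exp(i·2π·b·t/60)| over step times t in seconds, with b the cue tempo. R is 1 when the phase is constant and 0 when steps are spread evenly round the beat cycle.

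**Results at baseline 100, cue 110**

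| Walk | Change | Binary | D | Beats slipped | R |
|---|---|---|---|---|---|
| Steady 105 | +5% | adherent | 5 | 110 − 105 = 5 | 0.00 |
| Steady 109 | +9% | adherent | 1 | 110 − 109 = 1 | 0.00 |
| Steady 120 | +20% | adherent | 10 | 110 − 120 = −10 (ahead) | 0.00 |
| 30 s at 120, then 30 s at 100 (60 + 50 = 110 steps) | +10% | adherent | 0 | 0 net | 0.00 |
| Steady 110, every step half a beat off | +10% | adherent | 0 | 0 | 1.00, mean phase 180° |

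For the 109 row, 109 steps spread evenly round one beat cycle, so R is 0. Over baselines 90 to 120, the +5% walker slips 4.5 to 6.0 beats (R 0.00 to 0.07) and the +20% walker runs 9 to 12 beats ahead (R 0.00).

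The binary rule thus admits walkers who drift through several beats. D penalises the 105 and 120 walkers but gives a perfect score in the last two rows: it sees neither phase nor departures within the walk.

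**Would step-interval deviation from the beat interval repair this?** Only in part.
- Steady 109: 110/109 − 1 = 0.9%. Steady 105: 110/105 − 1 = 4.8%. These nearly repeat D (1 and 5 points).
- Half a beat off throughout: 0%, a perfect score.
- Half at 120, half at 100: (60 × 8.33% + 50 × 10%)/110 = 9.1%, so this case is caught.
- On the beat on average, with an assumed 4% normal step-time variation: 4% × √(2/π) = 3.2%, worse than the drifting 109 walker.

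**Reading a null.** With 60 recruited and 10% lost, n = 54. Using variance 1.06/(n − 3) on the Fisher z scale, an observed Spearman correlation of 0 has an unadjusted 95% interval of ±tanh(1.96 × √(1.06/51)) = ±0.28. A null is wide under any adherence measure.

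**The case against.** The best defence is that tempo matching is a declared and reasonable choice. The cue is itself a tempo, the Introduction's objective speaks of adhering to cues, and the cadence definitions are stated openly. Synchronising is used of participants only once, in the Discussion. Sustained synchrony also requires a cadence match, so cadence is a relevant proxy. All of this stands, and it is why a change of wording is enough.

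Stronger readings are tempting but not supported:

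- A reader might infer that every adherence analysis rewards off-beat walking. The Spearman analysis does not do so generally: it charges the +5% walker 5 points. A perfect score without following the beat needs an average that lands on +10%, and the half-120, half-100 walk is a constructed example.
- A reader might infer that nothing in the plan tests whether benefit depends on musicality. The second Gold-MSI analysis does so directly, without using adherence.
- A reader might infer a definite attenuation of the Gold-MSI correlation or loss of power. That needs the correlation between cadence deviation and true beat following, which the document does not give.
- A reader might infer that step-interval deviation would measure synchrony. It compares periods, ignores phase and takes in step-time variability, which the trial already studies as an outcome.

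**Conclusion.** The point holds in limited form. The stated construct (keeping to the beat, synchronising) is wider than what is measured (average tempo matching), and the Discussion's null conclusion goes beyond the adherence data. The demonstration uses the protocol's own rules plus an assumed baseline of 90 to 120 steps/min and the inference that cadence is one value per walk. Within that range, a walker at the +5% threshold is classed as adherent while slipping 4.5 to 6.0 beats. These are examples of what the measures cannot see, not estimates of how often it will happen. The objective is secondary in the Introduction and exploratory in the Discussion, and the primary gait comparisons are unaffected.

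**What to change.** 1. In Data collection item (viii) and in the Discussion's Exploratory objectives, replace adherence to the beat and synchronising with *match the cue tempo on average*.
2. Limit the null conclusion from the adherence analysis to tempo matching.
3. Base any statement about the success of music cueing on the second Gold-MSI analysis (against gait speed, stride length and stride-time variability changes), reporting confidence intervals so that an imprecise null is not read as no relationship.
4. If a synchronisation claim is to be kept, add a step-to-beat phase measure where recorded step times can be aligned with cue beats, such as the circular resultant length R with the mean phase angle. R alone is 1 for a constant half-beat offset, so the angle is needed too.
5. Step-interval deviation may be reported as a supplementary period-matching measure, stating that it ignores phase and includes step-time variability.

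Items 1 to 3 change wording and interpretation only and need no new data. Item 4 costs more: the article describes no alignment of step times with cue beats, so its feasibility must be confirmed first.

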### Usability and practical implications

Usability is a critical aspect of this protocol, as the practical application of CuePD depends on its potential ease of integration into daily routines and the overall acceptance of the methods proposed by PwPD. This feedback will be evaluated using the SUS questionnaire, to substantiate that utilising a smartphone-based system to provide gait analysis and rehabilitation could be a more appealing and effective option, presenting it as a viable and accessible alternative to traditional methods.

### Potential limitations and future considerations

This study will be conducted in a controlled laboratory setting, which allows for precision in measuring gait characteristics. However, the lab environment may not fully replicate real-world conditions, where environmental variables and day-to-day changes in motor symptoms may influence gait. Equally, the short testing duration in the lab does not provide clarity on long-term adherence in daily life. Moreover, although the study will use two sources for recruiting participants, there may be some bias introduced due to the use of the DeNDRoN case register as some participants may be more likely to be already motivated to take part in research, may have higher education or health literacy.

Future studies will consider validating CuePD in home and/or community-based settings to assess its feasibility and effectiveness outside of the lab. Accordingly, examining CuePD beyond the lab will provide insights to long-term adherence. Additionally, the study focuses on PwPD who can walk unaided, which may limit the generalisability of the findings to those with more advanced PD and/or those prone to episodes of freezing. Expanding future research to include these populations will be important to ensure CuePD’s broad applicability.

## Conclusion

The CuePD protocol will provide evidence for the validity and usability of a smartphone based approach to gait rehabilitation in PwPD. Its primary objectives are to validate and evaluate the effects of personalised auditory cues on gait characteristics, establishing a rigorous framework for assessing changes in gait speed, stride length, and stride time variability. This study will also validate the accuracy of the CuePD system in assessing detailed gait characteristics. CuePD may offer a potentially more effective, engaging, and accessible alternative to traditional gait rehabilitation methods. This could significantly enhance the quality of life for PwPD, encouraging more consistent and long-term engagement in rehabilitation activities.
